### Other general equilibrium effects

There is a possibility that some of the outcomes of the programme cannot be observed because of the type of intervention and the sampling design. In particular, the programme is likely to benefit only a few farmers in each of the project villages and the number of project villages for the study may not be sufficient to perform project-control comparisons that are statistically significant. In addition, there is a risk of large fluctuations within the trial period, which would tend to increase the variability in the outcomes and process measures – and, hence, possibly fatally undermine the power of the study due to this increased variability. We developed two strategies to mitigate this risk. The first involved the design of the study: we worked with Ministry of Agriculture technical stakeholders to spread the intervention area across a broad range of agro-ecological zones across the country. More importantly though, we devised an analysis strategy that includes two different simulations of the potential impact: The first is a micro-simulation of the farm-level impact of the intervention. Using household data we can estimate production and profit functions and then simulate the impact on farmers’ income, factoring in the additional demand and changes in food prices. Changes in prices can be simulated or observed directly through surveys. Similarly, the impact on consumption can be simulated after the estimation of a consumption function using household data. The second exercise consists of a village level simulation using a computable general equilibrium model. In this case, data are collected in one or two villages in order to build a social accounting matrix (SAM) to be used to simulate the impact of the injection of liquidity in the village economy. The advantage of this approach is that it allows the simulation of the impact on the entire community via price and demand effects. This method could also be used to simulate the differential impact of the programme in a drought and in a surplus year.

## Heterogeneity of impact

Gender, age and geographic area are other relevant categories to analyse impact. The impacts of school feeding in different contexts are quite heterogeneous [30]. School feeding, for instance, has been associated with marked improvements in school participation of girls in rural areas with large gender disparities in access to education [31]. Small-holder farmers targeted by the program will in large proportions be women. From the educational perspective, school feeding impact has also been found to vary with pupil age, as household schooling decisions are also affected by the opportunity costs of education, that tend to change with gender and increasingage and [32].

The programme is targeted to disadvantaged groups. Main beneficiaries are:

•Children aged 6 to 17 attending primary school

•Poor, rural districts of the country

•Smallholder farmer households

The programme has a potential poverty inequality reduction impact at the national level. At the local level it has a potential poverty reduction impact, but the inequality reduction impact will depend on whether:

•The project will increase enrolment. Children going to school are likely to be from richer background and more accessible areas.

•The project will involve small farmers. The programme might rely on large farmers or traders for the provision of food.

## Cost effectiveness

Cost data will be collected retrospectively following an ingredients approach using a semi-structured questionnaire. The survey will be based on a standardised costing framework capturing capital (fixed) and recurrent costs incurred at the school level. The questionnaire will also cover both cash and in-kind contributions and will be used to estimate both financial and economic costs. Financial costs capture actual expenditures in terms of programme implementation on an annual basis. Economic costs included the opportunity costs of community members, teaching staff and other school level stakeholders involved in the school feeding service provision. Opportunity costs of the school staff and community members will be calculated using local pay scales. Capital costs will be annuitized over the useful life of all relevant school level assets using a discount rate of 3% as per World Bank recommendations. Annuitisation enables an equivalent annual cost to be estimated and reflects the value in-use of capital items, rather than reflecting when the item was purchased [33].

Process and output data covering the adequacy of the service delivery will be collected from monitoring visits on a quarterly basis using standardised data collection forms. Output data will be combined with the costs to provide estimates of cost-efficiency metrics, including costs per beneficiary, kilocalories, iron and vitamin A delivered. Sensitivity analysis will be undertaken to account for uncertainties in the economic evaluation. The figures obtained in this way will then be compared to figures calculated for other interventions.

Of particular interest is the cost-effectiveness of the community level/social accountability component of the intervention. The comparison between the HGSF+ and the regular GSFP is roughly equivalent to the comparison between a home grown school feeding project and a standard school feeding project. Many would expect HGSF to be cheaper and more cost effective because of lower transport costs. However, the alternative procurement source, its distance and affordability is unknown, and hence the difference in costs between the two programmes is an empirical question.

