**Figure 2 F2:**
[figure not shown]
Stylised food procurement process in the HGSF+ programme.

A working group composed of in-country stakeholders, including the Dutch Cooperation Agency (SNV), Catholic Relief Services (CRS), and WFP is currently working on the details of the package of “software” interventions to improve overall programme performance. This package will include:

•Training of mayors and CAPS. At the beginning of each school year a number of training events will be organised for Commune-level stakeholders, including mayors and CAP. The purpose of the training events is to improve service delivery on several accounts:

◦ The establishment of a monitoring system of programme activities

◦ The identification of formulas for the allocation of food to schools (currently the allocation is based on rough enrolment estimates, but enrolment is endogenous as it is driven by food provision, hence a flexible system of funds and food allocation based on ‘predicted’ enrolment needs to be put in place.)

◦ The illustration of methodologies for purchasing from smallholder farmers rather than from traders (formulation of bids, contracts, contingency plans and so on)

◦ Nutrition education and the importance of adequate nutrition for school children and smallholder farmers, for example, how to use the foods they grow or purchase to improve the nutritional status of all family members, including diet diversification, availability of staple and nutrient rich foods by season, food storage and safety, food processing and preparation.

•Training of CGS. Training events for CGS at the village level will be held periodically, on a monthly or quarterly basis, in every intervention village:

◦ Members of CGS will be given the instruments to efficiently implement the programme including basic accountancy skills, information on their rights and entitlements, and information on methods to raise complaints

◦ Participatory monitoring events will be periodically held at the village level. +Members of CGS, parent teacher associations (PTAs), and parents will be involved in participatory events where the programme performance will be monitored in close detail, suggestions for improvement will be proposed and complaints brought to the attention of project staff and CAPs.

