### Random assignment and manipulation of treatments

The evaluation will measure outcomes at the child, household and school level. Households and schools will be randomly assigned to the intervention. Three treatment arms are envisaged:

1) Control group. These are schools and households from villages where the intervention will not be implemented. The intervention will be delayed by at least two years in these villages, preferably without informing schools and households.

2) Regular school feeding programme group. These are schools and villages where the standard Government programme is implemented, with mayors responsible for the food procurement.

3) Home grown school feeding and social accountability group (HGSF±). These are schools and villages where the programme is implemented in addition to a capacity building component, including training of community-based organisations and local government on food procurement, nutrition education and feedback monitoring.

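### The costing stops at the school and community, while much of what distinguishes HGSF+ is delivered at commune level, so its incremental cost over the regular programme omits part of the package

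*Protocol article*

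**What the plan says.** The Cost effectiveness section describes a retrospective ingredients costing by semi-structured questionnaire, and sets its scope in three places. On the framework: "The survey will be based on a standardised costing framework capturing capital (fixed) and recurrent costs incurred at the school level". Economic costs cover the opportunity costs of "community members, teaching staff and other school level stakeholders involved in the school feeding service provision". For capital, "Capital costs will be annuitized over the useful life of all relevant school level assets". A further sentence names no level: "Financial costs capture actual expenditures in terms of programme implementation on an annual basis".

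The section then states its main interest: "Of particular interest is the cost-effectiveness of the community level/social accountability component of the intervention". It identifies this with the contrast between HGSF+ and the regular government programme, and leaves the direction of the cost difference to be found empirically.

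Under Random assignment and manipulation of treatments, the HGSF+ arm is the programme "implemented in addition to a capacity building component, including training of community-based organisations and local government". That section also says HGSF+ is carried out at commune level, with training and monitoring that work through mayors. The HGSF pilot section lists the contents of the package, beginning with: "At the beginning of each school year a number of training events will be organised for Commune-level stakeholders, including mayors and CAP". It adds a monitoring system, monthly or quarterly training of school management committees (CGS) in every intervention village, and participatory monitoring events in villages.

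**The concern.** The costing boundary and the cost question do not match. To cost HGSF+ against regular feeding, the analysis needs the resources used in one arm and not in the other. Many of these are spent above the school, by people the costing section does not name: mayors, CAP staff, trainers and those who organise the events. Their effects on enrolment, learning, income and accountability would be counted in full, while part of what produced those effects would not be costed.

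A government deciding whether to add the training package to a national programme would read this comparison. The planned cost-efficiency figures, such as cost per beneficiary, would carry the same omission for HGSF+.

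**Working it through.** The article states no cost of the package and no cost-effectiveness ratio, so there is no figure to reproduce. The check sets the package against the stated boundary and then works out the sign of the error.

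**Step 1: which HGSF+ ingredients fall inside the boundary?** The contents come from The HGSF pilot, the boundary from Cost effectiveness.

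- *Training of mayors and CAPs each school year.* Commune level. Outside: neither the events nor the officials' time is a school-level cost, and these officials are not among the named stakeholders.
- *Commune-level monitoring system.* Outside, for the same reason.
- *CGS training in villages.* Partly inside. Participants' time can enter as community members' opportunity cost. Trainers, materials, travel and organisation are not incurred by the school.
- *Participatory monitoring in villages.* Partly inside, on the same split between participants and project staff.
- *Buying from local producers.* Unclear. Any effect on price may show in the cost of food delivered to the school. Mayors' and traders' costs that are not passed into that price would not show.

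**Step 2: does another instrument bring the missing items in?** The mayors' questionnaire (Survey instruments) covers canteen funds received and paid, deliveries, procurement, supervision, and training and knowledge acquired. It lists no training or monitoring costs. The school questionnaire has a module on training and monitoring activities, also without stated costs. Public expenditure tracking follows canteen money from the centre to mayors, CGSs and suppliers, and is only suggested. None of the three is linked to the cost-effectiveness analysis.

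**Step 3: sign of the error.** For HGSF+ minus regular feeding, write

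true incremental cost = S + P + T

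where S is the difference in school- and community-level costs, including delivered food; P is the difference in procurement and transport costs not already in delivered food prices; and T is the cost of trainers and organisers, mayor and CAP training and commune-level monitoring.

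The stated framework measures S, so

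measured − true = −(T + P).

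T belongs to HGSF+ only and is above zero whenever the package is delivered, so leaving it out understates the increment by T. If the incremental effect E is positive, the cost-effectiveness ratio is too low by T/E on this account. P can have either sign; a negative P would offset some or all of the understatement.

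**Step 4: size.** T cannot be derived. The article gives no training or monitoring cost. A cost per school would also depend on how many schools share one commune's training, which is not stated either.

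**The case against.** The strongest reply has four parts.

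First, the article does not say that costs are taken exclusively at the school. The sentence on financial costs speaks of programme implementation without naming a level, and other instruments gather data on procurement, payments, supervision and training. This stands in part: useful data will exist. But the financial-cost sentence describes what the school-level questionnaire will estimate, and no text carries the other data into the costing.

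Second, part of the package is captured. CGS training and participatory monitoring take place in villages, and community time and in-kind contributions are counted. This stands. A reader might infer that hardly any of the package would be costed; the article does not support that.

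Third, a reader might infer that HGSF+ must come out as cost-saving because food is the same in both arms and the measured increment is therefore about zero. The article says otherwise. Changing the source of food is a purpose of HGSF+, the Markets section expects any price impact only at HGSF+ sites, and traders deliver to schools, so delivered prices may already contain transport. S may be positive or negative, and omitting T does not fix the sign of the total.

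Fourth, this is a condensed article, a final data analysis plan is still to be approved, and sensitivity analysis is promised. A missing list of cost lines would indeed be no finding. Here, however, the article states a scope three times, and that scope does not fit the comparison it singles out. A sensitivity analysis for unspecified uncertainties does not recover a cost category that was never collected.

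**Conclusion.** The concern holds in this form: the stated costing boundary leaves out trainer and organiser costs, mayor and CAP training with officials' time, and commune-level monitoring, and the HGSF+ increment over regular feeding is understated by that amount. This assumes that the boundary is applied as written and that the package is delivered.

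The size is unknown. Scaling from the national school feeding budget would not supply it: that allocation includes equipment, rehabilitation and construction, and any percentage for training would be a guess. The sign of the total cost difference is undetermined.

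Cost-effectiveness is not a primary outcome, and randomisation, power and the main effect estimates are untouched. The change is still worth making, because it bears on the cost comparison the authors single out.

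**What to change.** Extend the ingredients costing to commune, CAP and programme level in both feeding arms. Include training events, trainers, materials and travel; the time of mayors and CAP staff; monitoring and supervision; and procurement or transport costs not already in delivered food prices. State how commune-level costs are shared among the schools they serve. Take the training and monitoring lines from the accounts of the project running the package and, where available, use the mayors' questionnaire and expenditure-tracking data for procurement and payments. Report the HGSF+ versus regular incremental cost with and without one-off start-up costs.

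The price is some added cost collection. Because costs are gathered retrospectively, it need not alter the randomisation or the household sample. The article does not say that mayors hold records of training costs, so those lines should not depend on them. The training and monitoring lines will make HGSF+ look less favourable than under school-only costing.

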## Risks

Overall, the study involves very low risks for participants. The risks are related to the quality of the food service delivered by the national school feeding programme. Risks involve food hygiene, sanitation and preparation related issues. There is also a risk associated with the potential disruption in the service delivery that could undermine the potential impact. If parents believe a child is fed in school when in fact the food service is not functioning, then the child can be potentially worse off after the intervention, though possibly just for one or a few days. The study will examine these risks in detail and also identify and test strategies to minimize these risks operationally.

## Ethical clearance

Ethical clearance was obtained from the appropriate boards in Mali and at Imperial College, London. Meetings were held from the early stages in the study development with relevant Government Ministries both at central and decentralised levels to discuss the purpose, procedures and risks involved in the study. Informed consent was obtained from parents/guardians of children through written and verbal information provided before interviews.

### Trial oversight

The evaluation team will be guided by a steering group, including the Government of Mali’s coordination framework on school feeding, and the Ministry of Education and Ministry of Agriculture. An independent steering group of experts in evaluation, public health, agriculture and education provided peer reviews prior to the data collection and will be convened at completion of the study to approve the final data analysis plan.

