**Design:**

This is a field experiment planned around the scale-up of the national school feeding programme, involving 116 primary schools in 58 communities in food insecure areas of Mali. The randomly assigned interventions are: 1) a school feeding programme group, including schools and villages where the standard government programme is implemented; 2) a “home-grown” school feeding and social accountability group, including schools and villages where the programme is implemented in addition to training of community based organisations and local government; and 3) the control group, including schools and household from villages where the intervention will be delayed by at least two years, preferably without informing schools and households. Primary outcomes include small-holder farmer income, school participation and learning, and community involvement in the programme. Other outcomes include nutritional status and diet-diversity. The evaluation will follow a mixed method approach, including household, school and village level surveys as well as focus group discussions with small-holder farmers, school children, parents and community members. The impact evaluation will be incorporated within the national monitoring and evaluation (M&E) system strengthening activities that are currently underway in Mali. Baselines surveys are planned for 2012. A monthly process monitoring visits, spot checks and quarterly reporting will be undertaken as part of the regular programme monitoring activities. Evaluation surveys are planned for 2014.

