## Programme theory of the intervention

School feeding interventions linked to small-holder agriculture can have multiple goals in the following areas:

•Food security: supporting incomes of recipient households (those consuming food) and farmer households (those providing the food)

•Education: increasing school enrolment, attendance and reducing drop-out, and improving cognition and learning achievement

•Health: improving nutritional status of school age children

The impact of the intervention in each of the above areas occurs through a number of complex pathways. This section describes the pathways through which the programme is expected to operate. Though the evaluation of all potential effects of the intervention is beyond the scope of this study, a subset of outcome indicators for the evaluation will be selected based on: a) a knowledge gap specific to school feeding in Mali; b) knowledge gaps in the school feeding literature in general; c) feedback from peer reviewers and technical partners; and d) budget constraints.

Figure 3 illustrates in very broad terms the impact theory of school feeding on food security, education and health. School feeding affects educational outcomes directly by increasing enrolment, attendance and completion (line ‘a’ in the figure). It affects health directly by improving nutritional status (line ‘b’), this in turn has an indirect impact on education, as improving nutritional status has a positive impact on learning outcomes (line ‘d’). The intervention can also affect income directly by increasing households’ food security (line ‘c’). Finally, there are effects running through increased income, health and nutrition, and vice versa, as richer families are investing more in human capital and more educated and healthier adults are more economically productive. However, these latter effects only occur in the long term and certainly not before children have left school; therefore, we will not discuss them in the following design.

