## Design of the randomized evaluation

The national school feeding programme will be expanded in the regions of Mopti, Koulikoro and Kayes. These areas are among the most vulnerable of the country and offer a diversity of agro-climatic conditions and cropping patterns. Areas that are inaccessible for most of the year or in which there are serious security concerns were excluded from the study. The Ministry of Education has set clear criteria for the selection of the intervention areas. Priority is given to areas of food insecurity and vulnerability, poor enrolment rates (particularly of girls), poor presence of donors and of high community involvement. Similarly, criteria for the selection of schools include: schools with poor retention and completion rates (particularly of girls); schools with children from nomad and destitute families; schools with children with special needs; schools where one-third of class has to travel at least 3 km to reach the school; schools demanding canteens.

The impact evaluation is an integral component of the monitoring and evaluation activities of the national school feeding programme. The baseline survey is planned in intervention and control sites in 2012 and a follow-up is planned in 2014. By 2015 the control schools and community will be fully integrated in the intervention. We will consider the possibility of conducting further surveys in the following years building matched control groups in order to detect long term effects of the intervention on farmers’ productivity.

We discuss here two main elements of the evaluation approach: random assignment and manipulation of treatment; and threats to validity.

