## Methods of analysis

The analysis will follow the intention to treat approach as protocol and as treated, using econometric and simulation analysis, for all the relevant outcomes of the intervention. Impact will be assessed for the different treatment arms using regression analysis to account for potential confounding variables, using a “difference-in-difference” estimator.

As enrolment rates in Mali are very low in rural areas (around 30%), one problem in conducting this analysis is that school feeding may bring to school children of very poor backgrounds with poor nutritional status and cognitive abilities to start with. This problem can be overcome econometrically by controlling for such confounders during the data analysis.

A further difficulty of difference-in-difference analysis is serial correlation [28] resulting from unobserved factors affecting the outcomes that are themselves correlated over time and that produce auto-correlated errors and invalid standard errors. Serial correlation affects estimated standard errors and can lead to erroneous acceptance or rejection of null hypotheses but not the estimation of the effect size of the intervention. Thus, it may lead to erroneously finding or not finding a statistically significant impact of the intervention. See [29] for an illustration of how this problem can be addressed by calculating clustered standard errors, a procedure that is easily implemented using the Stata software. Clustered standard errors will also be employed in all cases in which correlated outcomes are observed within the same unit of analysis, for example, when the impact of the intervention is analysed at the school level and test scores within the school are obviously correlated. Similarly, clustered standard error will be used at the household level when the project is affecting more than one child within the same family as in the case of the impact on siblings that was discussed in Section Impact on nutrition.

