### Conclusions

The power analysis suggests that the study will be able to detect an increase in enrolment by 5%, a 0.2 difference in test scores and an increase in farmers’ incomes by 25% between the school feeding interventions and the control group. The study will be able to detect changes in enrolment by 6%, differences in tests scores by 0.3 and changes in income by 40% between the regular school feeding and the HGSF+ components of the intervention see (Table 7).

**Table 7 T7:** Summary table of values used in the power calculations

	**Enrolment**	**Test scores**	**Agricultural income**
Alpha	0.05	0.05	0.05
N (observations)	55	25	10
J (schools)	2	2	2
K (clusters)	58	58	58
Intra Cluster Correlation	-	0.15	0.25
Between sites variability	-	0.20	0.40

While the sample size is well suited to the analysis of programme impact on attendance rates and test scores, it is clearly insufficient for the analysis of income effects of the HGSF+ intervention. However, we hope to overcome this problem in two ways: by increasing statistical power through restricted randomisation and by focussing on intermediate outcomes rather than on household income, a variable that has large variance and high within cluster correlation. First, in order to increase statistical power we will adopt ‘restricted randomisation’ [25]. We will use the baseline data collected at the village and school levels to remove the randomisation outcomes that would result in an unbalanced comparison of project and control communes. The randomisation of the HGSF+ component of the project within the 58 communes will be performed only within the restricted sample of balanced randomisation outcomes. Second, we will analyse intermediate indicators of household income such as input use (labour and other farm inputs, such as land, seeds and fertiliser) and farm capital use like animal traction, tools and simple machinery.

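### Independent approval of the final analysis plan is set at study completion, after the endline data exist, and nothing requires it to precede access to arm-identified results

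*Protocol article*

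**What the plan says.** The Trial oversight section gives the independent steering group of experts two tasks. Before the surveys it "provided peer reviews prior to the data collection". Afterwards it "will be convened at completion of the study to approve the final data analysis plan".

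The timetable is in Design of the randomized evaluation: "The baseline survey is planned in intervention and control sites in 2012 and a follow-up is planned in 2014". The Design paragraph of the abstract agrees: "Evaluation surveys are planned for 2014".

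On what is to be analysed, the abstract names domains: "Primary outcomes include small-holder farmer income, school participation and learning, and community involvement in the programme". On how, Methods of analysis says: "The analysis will follow the intention to treat approach as protocol and as treated". I read the middle term as per protocol. On income, the Conclusions of Appendix 1 accept that the sample is too small for the HGSF+ income comparison and propose, as one of two responses, "focussing on intermediate outcomes rather than on household income".

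**The concern.** An independent body's approval of an analysis plan protects the conclusions only if it comes before anyone who shapes the plan can see results by arm. Here the stated moment of approval is the end of the study, when the follow-up data have been collected. If decisive choices are still open then, the outcome or analysis approach could be picked, even without intent, because of what it shows. A reader of the final report could not tell whether the headline result was planned or selected.

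This is not a complaint that the article omits detail that belongs in a statistical analysis plan. The article states when that plan becomes final, and the stated time is the problem.

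**Working it through.** The article gives no figure on this point, so the check sets its passages side by side.

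**1. Order of events.** Trial status has the baseline survey under way in April 2012. Follow-up is in 2014. Approval is at completion. Approval therefore comes after endline collection on any ordinary reading. The peer review came before data collection, but the article does not say that it approved or locked an analysis plan.

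**2. Could analysts know the arm?** No masking of analysts is stated. The household questionnaire asks about meals at school, the school questionnaire covers food procurement and training, and the mayors' questionnaire covers deliveries and training. Removing an arm code would therefore not hide the arm by itself.

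**3. What is already fixed.** Random assignment and manipulation of treatments fixes both contrasts: school feeding against control at school level, and HGSF+ against regular school feeding at commune level. Appendix 1 repeats them and gives each its own power calculation.

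**4. What is still open.**

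- *Outcome within a domain.* For schooling, Table 2 lists enrolment, attendance and completion, and the hypotheses add drop-out. The enrolment power calculation itself moves between enrolment and attendance. For learning, Table 2 lists language and maths scores. This choice matters: Appendix 1 reports an average standardised effect of 0.31 for maths and none for reading, and powers the trial on maths. Community involvement is named as primary, but Table 2 gives only parental monitoring and motivation, and it has no power calculation.
- *Analysis approach.* Three approaches are named together and none is called primary.
- *Income under HGSF+.* For this contrast Appendix 1 gives 17% power for a 15% rise and 50% for a 30% rise; 80% power needs a 40% rise. A non-significant income result is therefore quite likely unless the effect is large. The proposed substitutes are a family. Main hypotheses and outcome indicators names 4 inputs (labour, land, seeds, fertiliser), 2 investments (tools, machinery) and 3 market measures (marketed surplus, prices, markets). Appendix 1 adds animal traction. That makes 4 + 2 + 3 + 1 = 10 named examples, in lists worded as illustrations, with none designated to carry the question.

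**5. Putting these together.** Leaving such choices to a later plan would be ordinary in a journal article. The weakness is that the later plan becomes final, by the article's own rule, only when the data exist.

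**The case against.** The strongest reply is that approval at completion may mean after fieldwork but before analysis. The wording allows this, and the word for a final plan suggests that an earlier version exists. This stands in part: it rules out saying that error control is lost. It does not remove the point, because the text does not state the safeguard on which that reading depends.

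Four stronger readings are tempting, and the document does not support them.

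- *That the contrasts are open too.* They are not; the design and the power calculations fix both.
- *That outcome selection as a whole waits until 2014.* A reader might infer this from Programme theory of the intervention, where "a subset of outcome indicators for the evaluation will be selected based on" is in the future tense. But the criteria given there (knowledge gaps, peer and partner feedback, budget) belong to the design stage, and Table 2 largely records the result. What remains is the choice within a domain.
- *That the move to intermediate income indicators is driven by data.* Appendix 1 gives its reason in advance, namely low power for the HGSF+ income comparison. The move is legitimate; only the choice among the indicators is loose.
- *That the harm can be put as a false-positive rate.* A calculation over outcomes and contrasts measures how many tests are run. It gives the same answer whether the plan is approved early or late, so it does not measure this defect.

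It is also fair to say that not naming a primary analysis set is no fault in an article whose analysis plan is not shown. I use it only to show what the late approval leaves undecided.

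**Conclusion.** The point holds in a limited form. The article sets independent approval of the final plan at a time when the endline data exist, and states neither an earlier lock nor a requirement that approval precede access to arm-identified data. The primary outcome within each domain, the primary analysis approach and the intermediate indicators for the HGSF+ income question could therefore be settled with knowledge of the results. The confirmatory status of the conclusions is at risk; it is not shown to be lost.

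No numerical size can be attached, because the effect depends on who sees what before approval. Exposure is greatest for HGSF+ income, where power is low and the substitutes are many. The verdict assumes that completion means after the 2014 survey and that no separate lock exists outside the article. If a dated plan was locked earlier, or if the sponsor intends approval before analysis, a sentence saying so would answer the point. It should be corrected, but it does not call the randomised design into question.

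**What to change.** Change the Trial oversight sentence so that the independent steering group approves and dates the final analysis plan before any arm-identified endline data reach the analysts. Because several questionnaire items reveal the arm, the restriction should cover those items as well as the allocation code.

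The approved version should name:

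- the primary outcome or outcomes for each of the two contrasts;
- the primary analysis set, with the other two approaches as supporting analyses;
- the intermediate indicators that carry the HGSF+ income question.

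Anything added after that date is reported as exploratory. The group can still meet at completion to review adherence to the plan.

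The cost is one earlier meeting, one changed sentence, and less freedom to adapt the analysis after seeing the endline data. With baseline under way in April 2012 and follow-up in 2014, there is time to do this.
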